**Hypothesis**

The sentinel lymph node procedure can be safely omitted in clinically node negative breast cancer patients undergoing breast conserving therapy. This will lead to a decreased axillary morbidity rate, with non-inferior regional control, distant-disease free survival and overall survival.

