***d. Sample size calculation***

Sample size calculation for a non-inferiority design including clinically node negative breast cancer

patients treated with breast conserving therapy, who will be randomized between SLN procedure versus no further axillary staging is as follows: Our hypothesis is that clinically node negative patients treated with breast conserving therapy who do not undergo the SLN procedure will have a non-inferior regional recurrence rate compared to patients in the control group and should therefore be treated as such.

Prior data indicate a 5-year regional recurrence free survival rate of 99% for the control patient group. The expected true regional recurrence free survival rate for the experimental patient group is 96% (taking into consideration the higher morbidity rate caused by axillary treatment in the control arm), and a difference of more than 5% in favour of the control patient group (the upper limit of a one-sided 95% confidence interval) is not accepted. The expected regional recurrence free survival rates and the non- inferiority limit of 5% (delta) result in a sample size of 747 per arm, to be able to reject the null hypothesis that the rate for experimental and control subjects is inferior by at least 5%, with a probability of 0.8.

|  | **p1** | **p2** | **Alpha  (type I error)** | **Power** | **Epsilon (p1-p2)** | **delta** | **Sample Size**  **(per arm)** |
| --- | --- | --- | --- | --- | --- | --- | --- |
| **Non-Inferiority** | 0,96 | 0,99 | 0,05 | 0,8 | -0,03 | -0,05 | 747 |

When taking into account a lost to follow-up rate of 10%, **1644** patients need to be randomized. In the Netherlands, every year **14.000** female patients are diagnosed with invasive breast cancer. About 80 % is operated on primarily (when excluding patients treated with systemic therapy only, or patients with primary metastatic disease and frail elderly).

| 14.000 * 80% = **11.200** patients  Of these patients, 80% is cN0.  11.200 * 80% = **8.960** patients  In the Netherlands 54% of the patients are treated with breast conserving therapy and 46% undergo  mastectomy.  8.960 * 54% = **4.838** patients  With the now known interest in participating of 43 hospitals in the Netherlands, 59% of the patients will visit a study hospital.  4.838 * 59% = **2.854** patients  We expect an accrual rate of 30%  2.854 * 30% = 856 patients yearly  This means that **3 years** will suffice to include **1644 patients (including 10% lost to follow-up)** |

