***e. Study procedures - axillary morbidity rate and quality of life***

**Introduction**

Omitting the SLN procedure in clinically node negative breast cancer patients undergoing breast conserving therapy might positively influence the axillary morbidity rate and quality of life. Although the SLN procedure is less invasive compared to an axillary lymph node dissection, complications do not rarely occur; most reported are seroma, hematoma, anaphylactic reaction, lymphoedema, numbness, tingling and pain [12-14]. Severe lymphoedema occurs in still 8% of patients undergoing only this axillary procedure after a follow-up of only 3 years [16]. These findings however are influenced by other therapies, such as the breast surgery itself, breast irradiation or adjuvant systemic therapy. Patients in this study are randomized to undergo either the SLN procedure (either with or without completion axillary treatment) or no SLN procedure. All patients will undergo the same breast treatment (lumpectomy followed by radiation of the breast). The SLN procedure is omitted in the experimental study group. Our study will therefore be the first to provide precise information on the influence of the SLN procedure on the axillary morbidity rate and quality of life.

Further, not performing the sentinel lymph node procedure and thereby possibly leaving supposed tumour load behind, could negatively influence patient’s well-being, with more insecurity and anxiety towards their future. Though, a study showed that trait anxiety rather than the diagnosis breast cancer determined whether patients experienced a low quality of life [59].

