***j. Final statistical analysis***

Primary and secondary endpoints will be analysed per protocol and in the intention to treat population

after 5 and 10 years of follow-up. Primarily, uncorrected chi-squared statistics will be used to evaluate the null hypothesis, as described in chapter 6, section d ‘Sample size calculation’ on page 19. The chi- square test will be based on the Kaplan-Meier estimator, in case of censored data. Additionally, cox proportional hazards models and Kaplan Meier estimates will be used to analyse the outcome of both groups and to assess the univariable and multivariable association between prognostic variables, treatment and events, using the stratification factors. All statistical tests are 1-sided and a P value of 0.05 or less is considered statistically significant.

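### The blanket one-sided 0.05 rule in section 7.j does not fit quality of life, systemic therapy use or the prognostic-factor analyses

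*Protocol*

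**What the plan says.** Section 7.j sets its own scope: "Primary and secondary endpoints will be analysed per protocol and in the intention to treat population". It then names chi-squared, Kaplan-Meier and Cox methods, including univariable and multivariable associations with prognostic variables, and closes with "All statistical tests are 1-sided and a P value of 0.05 or less is considered statistically significant". No endpoint is exempted.

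The one-sided level comes from the primary design. Section 6.d sets a 5-point margin on 5-year regional recurrence free survival and judges it by "the upper limit of a one-sided 95% confidence interval".

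The other endpoints are described differently:

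- **Oncological secondary endpoints.** Section 4 makes distant-disease free survival, overall survival, local recurrence and contralateral cancer non-inferiority objectives. The hypothesis refers to a result "with non-inferior regional control, distant-disease free survival and overall survival".
- **Quality of life.** The introduction to section 7.e says that omitting the sentinel node procedure "might positively influence the axillary morbidity rate and quality of life". It then says that leaving possible tumour behind could harm well-being, "with more insecurity and anxiety towards their future".
- **Axillary morbidity.** Sections 4, 7.e and 9.c look only toward a decrease.
- **Systemic therapy use.** Section 7.a defines a percentage difference between the arms without a direction. Section 8.d lists a difference of more than 5%, also without direction, as a reason to discontinue.

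**The concern.** A one-sided test needs a direction that is chosen in advance and is the only one of interest. Non-inferiority with a margin meets that condition. A comparison that could matter either way does not.

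Applied to quality of life, systemic therapy use and the prognostic models, the sentence leaves two possibilities. If the direction is fixed toward benefit, the plan cannot formally declare the worsening that section 7.e itself raises. If it is not fixed in advance and ends up following the data, the nominal 5% is really 10%. For a factor with more than two levels, such as the three age groups used for stratification, a global test has no single side, so the rule cannot be applied as written.

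At stake is how the quality of life and treatment-use results can be read. These results bear on whether omitting the procedure benefits patients overall.

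**Working it through.** **1. Reproducing the planned sample size.** Inputs from section 6.d: "Prior data indicate a 5-year regional recurrence free survival rate of 99% for the control patient group"; 96% expected in the experimental arm; margin 0.05; one-sided alpha 0.05; power 0.80.

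- Variance term: 0.99 × 0.01 + 0.96 × 0.04 = 0.0099 + 0.0384 = 0.0483.
- Distance from the expected difference to the margin: 0.05 − 0.03 = 0.02.
- n per arm = (1.645 + 0.842)² × 0.0483 / 0.02² ≈ 746.5, rounded up to **747**. This matches the protocol.
- At one-sided 0.025, n = (1.960 + 0.842)² × 0.0483 / 0.02² = **948**, and 747 per arm would give 70% power.

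One-sided 0.05 is therefore the level on which the primary comparison was designed.

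**2. Direction not fixed in advance.** With critical value 1.645 usable on either side, the error is 2 × (1 − Φ(1.645)) = 2 × 0.05 = **0.10** per comparison.

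**3. Direction fixed toward benefit: quality of life.** Section 7.e aims for 1056 evaluable patients, equally divided, so 528 per arm. The documents give no effect size; 0.1, 0.2 and 0.3 SD are assumptions. In SD units, SE = √(2/528) = 0.0615. For a true harm d:

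- one-sided test toward benefit: the probability of a significant result is Φ(−d/SE − 1.645), and such a result would wrongly point to benefit;
- two-sided 0.05 test: the probability of declaring the harm is Φ(d/SE − 1.960).

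| Assumed harm | d/SE | One-sided toward benefit | Two-sided 0.05 |
| --- | --- | --- | --- |
| 0.1 SD | 1.62 | 0.0005 | 0.37 |
| 0.2 SD | 3.25 | 0.0000005 | 0.90 |
| 0.3 SD | 4.87 | below 0.000001 | above 0.99 |

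**4. Direction fixed the wrong way: systemic therapy use.** Take a 5-point difference (the size named in section 8.d), assumed base rates p of 30% to 70%, and 747 to 822 per arm (1644 / 2 = 822). SE = √[p(1 − p)/n + (p − 0.05)(1.05 − p)/n]. For p = 0.5 and n = 747, SE = 0.0258 and 0.05/SE = 1.94. The one-sided test facing the other way is significant with probability Φ(−1.94 − 1.645) = 0.0002; a two-sided test has power Φ(1.94 − 1.960) = 0.49. Over the whole assumed range, the figures are at most 0.0002 one-sided and 0.49 to 0.62 two-sided.

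**5. Price of two-sided testing when the effect is in the expected direction.** With 528 per arm, moving from one-sided to two-sided 0.05 lowers power from 0.49 to 0.37 at 0.1 SD, from 0.95 to 0.90 at 0.2 SD, and hardly at all at 0.3 SD.

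**The case against.** The other side has several good points.

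- **One-sided testing is right for much of the plan.** Section 4 frames four oncological secondary endpoints as non-inferiority objectives. A reader might infer that one-sided 0.05 should be confined to the single primary comparison. The protocol does not support that: judging those four by two-sided 95% intervals would hold them to one-sided 0.025, stricter than the primary endpoint. This stands, and the fix respects it.
- **The protocol does not expect effects both ways everywhere.** A reader might infer that it does so for morbidity and systemic therapy as well. For morbidity it expects only a decrease. For systemic therapy it is silent on direction, and section 3 cites a simulation in which recommendations changed in 1.0-3.6% of patients. Only for quality of life are both directions named, and even there section 7.e tempers the harm by citing a study in which trait anxiety, rather than the diagnosis, determined low quality of life.
- **Harm is not ignored.** Under section 8.c the DSMB reviews the study endpoints, adverse events and the systemic therapy difference every year, and the section 8.d criterion works in both directions. The gap is in formal testing only.
- **A data-driven direction would be a misuse.** The protocol does not plan it. But it also fixes no direction for these endpoints, so the 10% describes what the text leaves open.
- **Non-significant survival results.** A reader might fear that a P value above 0.05 will be presented as non-inferiority. The protocol nowhere says so, and secondary margins may stand in the SAP.
- **Error accumulating over many endpoints.** That is a multiplicity question. It depends on an assumed number of independent comparisons, and most of it would remain under two-sided 0.05 tests.
- **The SAP may settle quality of life.** Section 7.j names only event-type methods. Yet its sentence is unconditional and its scope includes the secondary endpoints, so a two-sided SAP would contradict the protocol.

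**Conclusion.** The point holds in limited form. As a rule for all tests, one-sided 0.05 is wrong for quality of life, systemic therapy use and the prognostic-factor associations. For these, it either leaves an unfavourable effect practically impossible to declare or carries 10% instead of 5% error per comparison. Axillary morbidity is a milder case: one-sided testing matches the stated hypothesis, but an unfavourable result would go formally untested.

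The 10% is exact under the normal approximation. The power figures rest on assumed effects of 0.1 to 0.3 SD, on 528 evaluable patients per arm, and on assumed systemic therapy rates of 30% to 70%; none of the effect sizes or rates is in the protocol. The primary comparison, its 747 per arm and the non-inferiority framing of the oncological endpoints are not called into question.

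**What to change.** Replace the last sentence of section 7.j with two rules:

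1. One-sided 0.05 applies to the non-inferiority comparisons: regional recurrence, and those secondary non-inferiority objectives in section 4 for which a margin is fixed before the data are seen.
2. Quality of life, axillary morbidity, systemic therapy use and the prognostic models are tested two-sided at 0.05 and reported with two-sided 95% confidence intervals.

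The SAP should carry the same wording. The cost is an edit to one sentence and some power to declare the expected morbidity decrease: about 4 to 5 percentage points for an assumed effect of 0.2 SD, and about 12 for 0.1 SD, if morbidity is scored on the same 528 per arm. The primary sample size stays at 747 per arm.

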**8. SAFETY REPORTING**

***a. Section 10 WMO event***

In accordance to section 10, subsection 1, of the WMO (In Dutch: Wet Medisch-wetenschappelijk

Onderzoek met mensen), the investigator will inform the subjects and the reviewing accredited METC if anything occurs, on the basis of which it appears that the disadvantages of participation may be significantly greater than was foreseen in the research protocol. The study will be suspended pending further review by the accredited METC, except insofar as suspension would jeopardize the subjects’ health. The investigator will take care that all subjects are kept informed.

***b. Adverse events***

**Adverse events**

Adverse events (AE’s) are defined as any undesirable experience occurring to a subject during the study, whether or not considered related to the protocol treatment. All AE’s reported spontaneously by the subject or observed by the investigator or his staff will be recorded.

**Serious adverse events**

A serious adverse event (SAE) is defined as an untoward medical occurrence or effect related to protocol treatment that results in:

- death;
- hospitalisation or prolongation of existing inpatients hospitalisation;
- surgery.

Protocol treatment is defined as breast conserving surgery of the primary tumour, whole breast radiotherapy, SLN procedure, and completion axillary treatment. Any other operation or adjuvant treatment (such as chemotherapy) is not considered protocol treatment.

Information about SAE’s that occur within 30 days after protocol treatment is collected and recorded on the Serious Adverse Report Form. The principal investigator of the participating centre where the SAE occurs is responsible to report the SAE by e-mail to the central data centre (IKNL Clinical Trial Centre) within 24 hours.

The Principal Investigators (“verrichter” in the terminology of the Dutch law) are responsible for SAE assessment and expedited reporting through the web portal *ToetsingOnline* to the accredited METC that approved the protocol. The expedited reporting will occur not later than 15 days after the sponsor has first knowledge of the adverse reactions. For fatal or life threatening cases the term will be maximal 7 days for a preliminary report with another 8 days for completion of the report.

All SAE’s will be followed until they have abated, or until a stable situation has been reached. Depending on the event, follow-up may require additional tests or medical procedures as indicated and/or referral to the general physician or a medical specialist.

***c. Data Safety Monitoring Board (DSMB)***

An independent DSMB will be established comprising an independent surgeon, medical oncologist,

radiation oncologist, and statistician. The DSMB will meet annually to discuss the occurrence and nature of regional recurrences, other events (described in chapter 7, section 7.a ‘Study endpoints’ on page 21), the occurrence of AE’s, and the percentage difference in administration of adjuvant systemic therapy between both study arms. During the study, the DSMB may decide to change the frequency of discussion. All cases with a lesion that is highly suspicious for tumour recurrence on imaging, but not accessible for histology or cytology are presented to the DSMB for an independent review. An interim analysis is performed by a statistician, and results will be presented to the DSMB for further interpretation. Rules for the interim analysis will be described in the Statistical Analysis Plan. As

described earlier, premature termination of the study will not directly lead to additional axillary treatment of patients in study arm B, but only in case nodal metastases become clinically apparent during follow- up.

Advice(s) of the DSMB are send to the principal investigators. Should the principle investigators decide not to fully implement the advice of the DSMB, the principle investigators will send the advice to the reviewing METC, including a note to substantiate why (part of) the advice of the DSMB will not be followed.

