**Main study endpoint**

⮚ *Regional recurrence rate*

Regional recurrence is defined as tumour recurrence and as residual tumour that became clinically

apparent in ipsilateral axillary, infraclavicular and supraclavicular lymph nodes (pathologically proven).

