internal mammary lymph node chain (lymph nodes in the intercostal spaces along the edge of the sternum in the endothoracic fascia). Other-regional recurrence free interval is defined as the time interval between the date of randomization and the date of first clinical suspicion of other regional recurrence, measured in days.

⮚ *Contralateral breast cancer rate*

The occurrence of (pathologically proven) contralateral invasive breast cancer will be registered. Contralateral breast cancer free interval is defined as the time interval between the date of randomization and the date of first clinical suspicion of contralateral breast cancer, measured in days.

⮚ *Diagnosis of recurrence outside the axillary region*

One or more of the following must be positive for the diagnosis of tumour recurrence to be accepted:
I. Histology or cytology

II. Autopsy examination

Diagnosis based on radiological findings can be considered if I or II is not possible/available (these
cases will be presented to the Data Safety Monitoring Board (DSMB) for an independent review).

⮚ *Percentage difference in the administration of (neo)adjuvant systemic therapy*

This is defined as the percentage difference in the administration of (neo)adjuvant systemic therapy

between both study arms.

- *Quality of Life*

Quality of Life will be assessed using validated questionnaires, as shown in chapter 7 ‘METHODS’, section e ‘Study procedures - axillary morbidity rate and quality of life’ on page 27.

⮚ *Axillary morbidity rate*

The axillary morbidity rate will be assessed using validated questionnaires, as shown in chapter 7

‘METHODS’, section e ‘Study procedures - axillary morbidity rate and quality of life’ on page 27.
⮚ *Cost-effectiveness*

The cost-effectiveness will be assessed by using patient questionnaires, as shown in chapter 7 ‘METHODS’, section f ‘Cost-effectiveness analysis’ on page 28 and electronic Case Report Forms (eCRF) as shown in chapter 10 ADMINISTRATIVE ASPECTS AND PUBLICATION on page 34.

1. ***Study procedure – diagnosis and randomization***

*Diagnosis*

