***i. Premature termination of the study***

After premature termination of the study, the investigators must contact all participating subjects within

4 weeks. No new patients are included in the trial. Follow-up of participating subjects will continue, following the study protocol. In case of premature termination of the study due to a higher regional recurrence rate than expected as determined by the DSMB, this will not have a direct consequence for the treatment or follow-up of every study patient that has been randomized for study arm B. So in these patients, delayed axillary treatment is not standardly performed, but only if nodal metastases become clinically apparent.

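### Imaging-only recurrences are reviewed by the board that also receives the interim results, with no masking to arm required; the main exposure is distant-disease free survival

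*Protocol*

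**What the plan says.** Section 8.c of the protocol gives the Data Safety Monitoring Board (DSMB) three tasks.

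- Regular review of events: "The DSMB will meet annually to discuss the occurrence and nature of regional recurrences, other events", together with adverse events and the between-arm difference in systemic therapy.
- Interim results: "An interim analysis is performed by a statistician, and results will be presented to the DSMB for further interpretation".
- Single cases: all lesions highly suspicious on imaging but "not accessible for histology or cytology are presented to the DSMB for an independent review".

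Section 7.a repeats the third task under the heading "Diagnosis of recurrence outside the axillary region". Recurrence normally needs histology, cytology or autopsy. Then: "Diagnosis based on radiological findings can be considered if I or II is not possible/available", and these "cases will be presented to the Data Safety Monitoring Board (DSMB) for an independent review".

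Section 7.i adds that the board judges the running recurrence rate: "In case of premature termination of the study due to a higher regional recurrence rate than expected as determined by the DSMB".

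The primary endpoint in section 7.a is limited to nodal disease that became clinically "apparent in ipsilateral axillary, infraclavicular and supraclavicular lymph nodes (pathologically proven").

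**The concern.** A lesion that cannot be sampled is the kind of event most open to judgement. The protocol describes its review as independent. The board is independent of the investigators, but it is not independent of the accumulating data, because it also interprets the interim analysis. Someone who knows the patient's arm, or the running difference between arms, may be readier or slower to accept an equivocal lesion. The bias can go either way. In a non-inferiority comparison, under-calling events in the study arm favours the trial's claim and over-calling them works against it.

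Blinding does not help, since one arm has sentinel node surgery and the other does not, and the protocol describes no masking of anyone. What is at stake is the credibility of any endpoint that an imaging-only lesion can enter.

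**Working it through.** This is a question of procedure. The protocol gives no figure for it, so there is nothing to recompute. The check sets the provisions side by side.

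**Step 1. Are the two roles held by one body?** Yes. Section 8.c gives interim results and review of single cases to the same DSMB, and section 7.a confirms the second role. The protocol names no separate endpoint committee.

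**Step 2. Is this left to the statistical analysis plan?** Only in part. Section 8.c defers the rules for the interim analysis to that plan. Who reviews imaging-only cases is fixed in the protocol itself, with no condition on masking or order of work.

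**Step 3. Which endpoints can an imaging-only lesion enter?** From the definitions in section 7.a:

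| Endpoint | Pathology required by its definition? | Imaging-only lesion can enter as written? |
| --- | --- | --- |
| Regional recurrence (primary) | Yes | No |
| Regional recurrence free survival | Dated from first suspicion; the event is regional recurrence as defined above, or death | No, if the primary definition is applied |
| Local recurrence | Yes | No |
| Other-regional (internal mammary) recurrence | Yes | No |
| Contralateral breast cancer | Yes | No |
| Distant-disease free survival | No; dated from first suspicion of distant recurrence, or death | Yes |
| Overall survival | Not a recurrence endpoint | No |

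Distant-disease free survival is therefore the one endpoint clearly exposed. It is not a minor one: section 4 lists it first among the secondary non-inferiority objectives, and the stated hypothesis claims non-inferiority for it.

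**Step 4. Do the provisions agree with each other?** Not fully. The imaging route in section 7.a covers recurrence outside the axillary region. Read widely, that takes in the ipsilateral breast, the internal mammary chain and the contralateral breast, all of which need pathology under their own definitions. It could even be read to take in the infraclavicular and supraclavicular nodes, which belong to the primary endpoint. Section 8.c drops the regional limit and sends every suspected recurrence that cannot be sampled to the board. Neither place says what happens when the imaging route meets an endpoint that requires pathology.

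**Step 5. Size.** An estimate would need the expected number of distant recurrences and the share that cannot be biopsied. The protocol gives neither, so no figure is offered.

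**The case against.** The strongest reply has four parts.

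- **Silence is not evidence of unmasked review.** The protocol never says that the review is unmasked, or that recurrences are tabulated by arm; in section 8.c the comparison between arms is attached to systemic therapy. A DSMB charter or the analysis plan, neither of which is shown, may set masking and order of work. This stands as a limit on the claim: the defect is that masking is not required, not that it is known to be absent. By-arm interim results are still the natural reading for a two-arm non-inferiority trial, and the protocol points to no charter.
- **The board may not decide.** The text speaks of review, says that a radiological diagnosis can be considered, and calls the board's output advice that the principal investigators may decline. That also stands. A binding ruling is a possible reading but is not written. Even so, no other body is named to review these cases.
- **The primary result is safe.** A reader might infer that a few reclassified lesions could swing the primary comparison, since few events are expected: at the design rates of section 6.d, 747 × 0.01 ≈ 7.5 in the control arm and 747 × 0.04 ≈ 29.9 in the study arm. The documents do not support this. An imaging-only lesion is by definition not pathologically proven, so it does not meet the primary definition. The same holds for local, other-regional and contralateral events.
- **Stopping advice is barely touched.** A reader might also infer that the board's advice rests on events it classified itself. The recurrence ground in section 7.i is the regional recurrence rate, which requires pathology, and the numerical trigger in section 8.d concerns systemic therapy. Imaging-only distant lesions could enter only through the board's general advice.

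**Conclusion.** The point holds in a limited form. The protocol gives review of imaging-only recurrences to the board that also discusses accumulating events and receives interim results. It does not require that review to be masked to arm or completed before by-arm data are seen. This leaves classification of unproven distant recurrences open to bias in either direction, with distant-disease free survival as the main exposure.

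The conclusion rests on three assumptions: that the interim results shown to the board are by arm, that its view carries weight in classification, and that no document outside the protocol already requires masking. The first two are likely but not stated; the third cannot be checked here. The effect on distant-disease free survival cannot be quantified. No effect on the primary endpoint is claimed, provided that its pathology requirement is applied as written.

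**What to change.** 1. State in sections 7.a and 8.c that imaging-only cases go to the clinical members of the DSMB as packs masked to arm. The packs hold the imaging and clinical course, with the allocation, operation report and axillary treatment removed.
2. State that each classification is recorded and locked before that meeting's by-arm data are opened, and is not revisited afterwards.
3. Reconcile the unrestricted referral in section 8.c and the imaging route in section 7.a with the endpoint definitions. State that imaging-only lesions do not count towards endpoints defined as pathologically proven.

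The cost is a short wording change and a little preparation by the data centre. It needs no extra readers and no change to sample size or patient care. Two limits remain. Post-operative change on imaging may occasionally reveal the arm. And from the second meeting on, members will know the balance shown earlier, so protection then rests mainly on the masking of the packs. A separate endpoint committee masked to arm would remove the second limit, but it would need additional readers.
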